#### 11.10 Support for adherence

Partners in a couple will serve as the PrEP and TasP adherence supports for each other. Participants will be reminded of the need to take their drugs through the use of sms messages sent to their telephones. The Nigerian Communications Commission (NCC) reports a mobile phone subscription rate of 94.7% with a national teledensity of 72.3 as of May  (Teledensity is the number of telephones per 100 people.) Notably, there has been a sustained upward trajectory of mobile phone subscribers, and the teledensity is expected to exceed 100 within the next three years. This means that mobile phones are already very common; so this intervention will not require additional infrastructure. Computer based monitoring systems are user friendly, culturally appropriate, and convenient for the target population, as they can use their personal mobile phones. We expect that this intervention will increase adherence to daily schedules for PrEP use, refill appointments and clinic schedules. It is expected to be an effective and cost-efficient intervention.

#### 11.11 Support for HIV positive partners

Conventional approaches for supporting HIV positive clients in the study sites will be adopted for this study. This would include: ongoing HIV counseling and risk reduction counseling in line with the National guidelines; couples counseling, and counseling on family planning and child bearing. Clients will also be referred to support groups. These conventional approaches will be augmented with the use of sms reminders for drug adherence for all study participants who opt for use of TasP for HIV prevention.

#### 11.12 Suspending or discontinuing PrEP

Study participants will be discontinued from using PrEP by the Principal Investigators and their designees in the event that they experience a Serious Adverse Event (SAE) that is judged by the study clinician or designee to be related to PrEP use (see Section 8.2). Pregnancy will not be an indication for the discontinuation of the drug because risk of HIV transmission is high in pregnancy, and the study drugs are not contraindicated in pregnancy.

For participants who temporarily discontinue PrEP use, every effort will be made to complete all procedures specified in the protocol (except study product dispensing procedures). Designated staff will document all changes in PrEP regimen, and the reason for the change, on applicable Case Report Forms (CRFs).

---

59 Nigerian Communications Commission. 2012. Subscriber Data. <http://www.ncc.gov.ng/industry-statistics/subscriber-data.html>. Accessed, July 2012.

60 Curioso WH, et al. Design and Implementation of Cell PREVEN: A Real-Time Surveillance System for Adverse Events Using Cell Phones in Peru. AMIA Annu Symp Proc 2005; 176-180

### 11.13 Concomitant medications

Enrolled study participants may continue use of all concomitant medications, including prescription, nonprescription, traditional, and other preparations during this study. All concomitant medications used by participants during the study will be reported on applicable CRFs.

## 12.0 Safety

### 12.1 Adverse events and reporting requirements

An AE is defined as any untoward medical or social occurrence in a clinical research participant whether or not it has a causal relationship with the study product. (Study product refers to Truvada pills.) Information regarding symptoms or conditions that occur during the screening period will be recorded in the participant's medical history as pre-existing conditions. All new or worsening symptoms or conditions that occur following randomization will be considered AEs and will be recorded on the appropriate CRF.

### 12.2 Adverse event reporting

Study participants will be provided contact telephone numbers and instructed to contact study staff to report any AEs they may experience, except for life-threatening events for which they will be instructed to seek immediate emergency care. Depending on the severity of the event, the study staff will instruct the participant to present to their assigned study site (for mild events) or to a hospital casualty department (for serious events) for immediate evaluation. With appropriate permission of the participant, records from all non-study medical providers related to AEs will be obtained and required data elements will be recorded on study CRFs. All participants reporting an AE will be followed clinically, until the AE resolves (returns to baseline) or stabilizes. AEs that are ongoing at the time of study exit will be followed up for up to 30 days after study exit and then, if not resolved, will be referred to a health care provider for further follow-up. Designated study staff will determine the severity of the AE and document it on the appropriate CRF. Each adverse event that the participant is aware of will be graded for severity using the most current DAIDS severity grading system.

For each AE, an assessment of the relatedness to the study product will be made using the criteria and scale as outlined in the SSP manual. All AEs will be captured regardless of the association or otherwise to PrEP and reported on the appropriate CRF in accordance with the SSP. All AE reports will contain at least the date the AE occurred, a brief description of the event, the relationship to study product, the action taken, the outcome, date resolved, and the seriousness of the event.

### 12.3 Serious adverse event (SAE) reporting

An SAE includes any experience that is fatal or life-threatening, results in persistent or significant disability/incapacity, requires or prolongs hospitalization, or is a congenital anomaly. A life-threatening AE means that the participant was, in the view of the designated study staff, at immediate risk of death from the condition as it occurred. Notification of deaths will be recorded by reflecting the medical condition that led to the

death on the appropriate CRF. Reporting SAEs may require additional detailed reports and follow-up. All serious adverse events will be reported to Gilead, the National Agency for the Food and Drug Administration and Control (NAFDAC) and the National Health Research Ethics Committee (NHREC).

#### 12.4 Safety monitoring

Designated study staff will be responsible for continuous close safety monitoring of all study participants. The study statisticians will prepare routine study progress reports for review by the Protocol Team. In addition, the study statisticians will prepare routine study progress reports which include reports of AEs experienced by study participants.

### 13.0 Data management and analysis

#### 13.1 Data analysis

A Statistical Analysis Plan (SAP) will be developed. This will outline the planned analyses. Any deviations to be made from the plan will be documented in the SAP.

For the primary objective 3.1.1, the outcome variable to be measured will be the uptake of antiretroviral-based HIV-1 prevention program. Data collected will include all sero-discordant couples recruited into the study and will be followed up longitudinally. The number of new infections averted through the use of PrEP and TasP by sero-discordant couples who accessed the ARV preventions compared with those who had access to programs but did not use the tools will be documented. The impact of various variables such as age, viral load of partner, region, coital act, use of condom on uptake of PrEP and TasP and on HIV sero-conversion will also be assessed.

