study also revealed that this finding was attributable to the poor adherence, since the drug was only detectable in less than a quarter of participants assigned to the treatment group. More importantly when looking at the characteristics of the non-adherent participants, it appears that they were more risky groups, adherence was poorer among women under 25 years and among unmarried women. Thus, while a number of factors could explain the divergent trial results, foremost being non-adherence. Importantly, for HIV-1 uninfected members of known HIV-1 serodiscordant couples, as shown in the Partners PrEP Study, adherence appears to be very high.

Although perception of risk has been found to be a main predictor of health behaviours, only one study has focused on the effect of risk aversion on perceived risk of HIV and HIV status. Further research is then needed in order to investigate the role of risk aversion on adherence to PrEP.

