### 3.0 Objectives

#### 3.1 Primary objectives

- 3.1.1 Optimize, implement and evaluate the effectiveness of an implementation model which integrates PrEP and TasP provision into existing service provision centres.
- 3.1.2 Estimate the cost and cost effectiveness of the PrEP and TasP demonstration project.
- 3.1.3 Model the resources needed to provide scaled up PrEP and TasP access for serodiscordant couples in Nigeria.

**Objective 3.1.1: To optimize, implement and evaluate the effectiveness of an implementation model which integrates PrEP and TasP provision into existing service provision centres.**

The demonstration project will be evaluating the effectiveness of a model of HIV service delivery to couples that promotes and ensures effective PrEP access. Such a model should be able to ensure effective community engagement in ways that improve and support a couple's access and uptake of HIV prevention and treatment interventions, ensure access in hard to reach areas where there are few health facilities, and support sustained quality and consistency of PrEP and TasP services irrespective of place of delivery. The model for delivery of ART based HIV intervention programs for couples for this demonstration project would be designed based on feedback received during the formative research conducted to support this research. The study outcome should help critical stakeholders know how well the study model was able to achieve the desired PrEP service delivery into family planning services. This will help inform decision making on how to institutionalize the program, strategies that are economical and efficient, and how best to make modifications to the program implementation model to increase effectiveness.

The primary outcome of this objective is the measure of the impact that project intervention had on serodiscordant couples' access, uptake and retention in the antiretroviral-based HIV-1 prevention program. Formative and summative evaluations would be conducted. Formative evaluation will be conducted at months 6, 12 and 18 with derived information use to modify the program so as to increase its efficiency. The summative evaluation will be conducted at the end of the project and would help to decide on the effectiveness of the program.

*The primary measure of this objective will be the number of new infections averted by the use of PrEP and TasP.*

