**Objective 3.1.2: Estimate the cost and cost effectiveness the PrEP and TasP demonstration project.**

A critical aspect of implementation is to obtain estimates of the cost of implementing PrEP on a small scale. Incremental financial and economic costs of provision will be collected from the provider's perspective for the duration of the demonstration project. Financial costs represent actual project expenditures, while economic costs represent the full value of all resources used in the intervention. Effectiveness will be modelled based on the Nigerian epidemic and intermediate demonstration trial outcomes to provide life years gained and infections averted. These will be matched with costs to estimate the cost effectiveness of the intervention in terms of cost per life year gained and cost per infection averted. Patient travel and opportunity costs will also be collected. This will provide insights into the travel costs incurred by the project to support transportation of study participants from satellite sites to the main study sites as well as other costs of participation

*The primary measure of this objective is cost per life year gained and cost per infection averted.*

**Objective 3.1.3: Model the resources needed to provide scaled up PrEP and TasP access for serodiscordant couples in Nigeria.**

While objective 3.1.2 will provide insights into the cost-effectiveness at demonstration project scale and target population level, this objective will enable the team make projections on what the real cost of scaling up the project will be. We will model the cost of a national PrEP program targeting serodiscordant couples. Using the cost data generated during the demonstration project, a cost model will estimate the total financial resources needed to scale up to a regional or national program as deemed appropriate. Further analysis will be undertaken to explore non-financial constraints such as personnel and infrastructural constraints.

*The primary measure of this objective is an estimate of the total budget necessary to scale up PrEP and TasP nationally within the various target groups.*

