## 8.0 Sample Size

A total of 600 couples will be enrolled from the three study sites. Enrollment will be competitive. All couples will participate in the longitudinal cohort study. A subset of up to 60 couples per site will be invited to participate in qualitative in-depth interviews and focus group discussions.

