#### 11.4 Recruitment, screening and enrollment

Eligible participants will be enrolled over approximately 12 months. At regular intervals, the Principal Investigators, in consultation with the study team, will assess progress in accrual and retention at each of the sites and may reallocate enrollment numbers and targets across the sites, as deemed necessary to achieve the goals of this trial efficiently. All potential participants will be screened, enrolled and escorted to the respective family planning services, for completion of enrollment visit procedures.

At screening, demographic and behavioral information will be collected, along with laboratory results to establish the risk score and participant eligibility (for HIV-1 uninfected partners – serum creatinine, hepatitis B surface antigen; for HIV-1 infected partners – CD4 count, plasma HIV-1 viral load; for both partners – HIV-1 rapid testing according to national algorithms).

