For participants who are initially uninfected but who seroconvert during the study, PrEP will be discontinued. Their blood specimen will be taken and drug resistance profiling will be conducted. This is to assess if any drug resistance has developed to Truvada and what drug regimen the study participant is sensitive to. Seroconverters will have a visit within 1-month after they seroconvert and then follow-up in the study will be completed for both members of the couple. These visits will include risk reduction and contraceptive counseling, collection of behavioral and medical history data during one-on-one interviews, and collection of blood specimens for assessment of CD4 count, HIV-1 plasma viral load levels from both partners and HIV resistance profiling. Those who seroconvert will be enlisted to have access to ART whenever (s)he is ready to start drug treatment.

Interim visits may occur at any time during the study. All interim contacts and visits will be documented in participants' study records and on applicable CRFs. If a study participant presents to an interim visit with symptoms suggestive of acute HIV-1 infection syndrome, rapid HIV-1 testing will be performed, as at a scheduled visit, and study medication will be withheld if a positive rapid test is documented.

HIV-1 testing for index (HIV-1 infected) participants at screening and for partner (HIV-1 uninfected) participants at screening, enrollment, and follow-up – will be performed in line with national HIV-1 testing algorithms for Nigeria. HIV-1 seroconversions will be

confirmed using HIV-1 EIA. HIV-1 testing will be accompanied by couples and/or individual counseling, depending on attendance of the index (HIV-1 infected) participant at a study visit. All counseling and testing approaches will be in accordance with national HIV-1 counseling and testing guidelines.

Participants infected with hepatitis B virus (HBV) at enrollment will be closely monitored clinically and using laboratory diagnostics especially during episodes of product hold. Any participant needing further treatment for HBV will be referred to a health care provider for further follow-up.

All data collection will be conducted in a private room in the participant's preferred language, according to the participant's fluency and preference.

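### Infections averted is to be read from couples who used PrEP or TasP against couples who chose not to, a self-selected comparator that can show a benefit when there is none

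*Protocol*

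**What the plan says.** Under objective 3.1.1 in section 3.1 of the protocol: "The primary measure of this objective will be the number of new infections averted by the use of PrEP and TasP". Section 13.1, in its paragraph on that objective, gives the contrast. Infections averted among couples who took up the antiretroviral tools, "compared with those who had access to programs but did not use the tools will be documented". The same paragraph names a different outcome for the objective: "the outcome variable to be measured will be the uptake of antiretroviral-based HIV-1 prevention program". It then says that age, partner viral load, region, coital acts and condom use will be examined against uptake and against seroconversion, without tying them to the infections-averted contrast.

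For objective 3.1.2 the protocol takes another route: "Effectiveness will be modelled based on the Nigerian epidemic and intermediate demonstration trial outcomes to provide life years gained and infections averted".

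Four design features bear on who ends up as a non-user:
- Sections 2.0 and 11.5 offer PrEP to the uninfected partners and ART to index partners whatever their CD4 count.
- Section 2.0 keeps PrEP going where the index partner declines ART, so a non-user couple is one that takes neither tool.
- Section 11.5 has TasP counselling continue during follow-up, so use can begin well after enrolment.
- Section 11.5 also states: "For participants who are initially uninfected but who seroconvert during the study, PrEP will be discontinued". Follow-up of both partners then ends after a further visit within a month.

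Section 8.0 gives the size without a derivation: "A total of 600 couples will be enrolled from the three study sites".

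**The concern.** There is no randomised, untreated or historical group for objective 3.1.1. The comparator consists of couples who were offered everything and declined. Whatever leads a couple to decline (perceived risk, condom use, stability of the relationship, the index partner's viral load) may also affect the chance of infection, so a rate difference can arise with no effect of the tools.

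Two further weaknesses depend on facts that the protocol does not fix. Use is an event after enrolment, yet no time zero and no rule for classing a couple as user or non-user is given. If couples are classed by whether they ever used the tools, a late starter contributes infection-free waiting time to the users, while a partner infected before starting is counted among the non-users. And the non-user group shrinks as the programme succeeds in recruiting users.

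At stake is the effectiveness measure of a primary objective, and whether 3.1.1 and 3.1.2 report the same number of infections averted.

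**Working it through.** The protocol has no power or sample-size figure to reproduce.

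**Inputs from the protocol:** 600 couples (section 8.0); follow-up of up to 18 months (section 11.0), taken as 1.5 years with no loss; a PrEP efficacy of about 75% (section 1.4). **Assumptions:** uptake 70 to 95%; incidence 2 to 5 per 100 person-years without effective use; two-sided alpha 0.05.

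**1. Self-selection, with no true effect.** Let uptake be u = 0.90, overall incidence 0.03, and let non-users have k times the users' rate. Users' rate = 0.03 / (u + (1 − u)k). User person-time = 600 × 0.90 × 1.5 = 810 years. Infections apparently averted = (non-user rate − user rate) × 810.

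| k | user rate | non-user rate | rate ratio | apparent reduction | falsely averted |
|---|---|---|---|---|---|
| 1.5 | 0.0286 | 0.0429 | 0.67 | 33% | 11.6 |
| 2 | 0.0273 | 0.0545 | 0.50 | 50% | 22.1 |
| 3 | 0.0250 | 0.0750 | 0.33 | 67% | 40.5 |

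The bias can run the other way. With k = 0.5 the user rate is 0.03 / 0.95 = 0.0316 and the non-user rate 0.0158. The rate ratio is then 2.0, and −12.8 infections are averted.

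**2. Immortal time, with no true effect, under ever/never classing.** Let shares a, b and c of couples start at enrolment, start late and never start, and let late starters wait on average a fraction w of follow-up. To first order, for low incidence:

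rate ratio ≈ [1 − bw/(a + b)] / [1 + bw/c]

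| a / b / c (%) | late starts spread over | w | rate ratio |
|---|---|---|---|
| 30 / 50 / 20 | 18 months | 0.5 | 0.6875 / 2.25 = 0.31 |
| 80 / 15 / 5 | 18 months | 0.5 | 0.921 / 2.5 = 0.37 |
| 80 / 10 / 10 | 18 months | 0.5 | 0.944 / 1.5 = 0.63 |
| 90 / 5 / 5 | 3 months | 0.083 | 0.996 / 1.083 = 0.92 |
| 90 / 0 / 10 | none late | – | 1.00 |

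Simulation agrees (for example 0.63 for the third row, 0.91 to 0.92 for the fourth and 1.00 for the last). Splitting person-time at first use brings the ratio back to 0.99 to 1.01 in every simulated pattern. The split does nothing about self-selection.

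**3. Size of the comparator.** Expected non-user infections = 600 × (1 − u) × 1.5 × incidence.

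| uptake | non-user couples | person-years | infections at 2 to 5 per 100 person-years |
|---|---|---|---|
| 70% | 180 | 270 | 5.4 to 13.5 |
| 80% | 120 | 180 | 3.6 to 9.0 |
| 90% | 60 | 90 | 1.8 to 4.5 |
| 95% | 30 | 45 | 0.9 to 2.25 |

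Exact conditional power to detect a true 75% reduction at 3 per 100 person-years is 38% at 90% uptake and 25% at 95%. At 70% uptake and 5 per 100 person-years it is 86%.

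**4. The statements side by side.** Section 3.1 measures objective 3.1.1 by infections averted; section 13.1 names uptake as the outcome variable. Section 13.1 obtains infections averted from users against non-users; objective 3.1.2 obtains it from a model. Nothing in the protocol links the two routes.

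**The case against.** The strongest reply is that section 13.1 defers the analysis to an SAP, which may define time zero, split person-time and adjust. The covariates it would need are already listed in 13.1, and PrEP is offered at enrolment, so late starts may be few. The Summary presumes efficacy and disclaims any aim to establish it. This stands as far as person-time rules go: their absence from a protocol is not itself an error. It does not rescue the comparator, which the protocol has already chosen for a primary measure. Adjustment can reduce confounding but cannot be relied on to remove it.

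Several stronger readings are tempting and should not be drawn:
- **That the contrast is immortal-time-biased as written.** It is only open to that bias. The protocol does not prescribe ever/never classing, and the ratio is 1.00 if every user starts at enrolment.
- **That the comparator is very small.** That depends on an uptake which is not stated; near 70% it is not.
- **That the bias must favour the programme.** Section 1.2 does say of poor adherers that "it appears that they were more risky groups", but this describes women assigned product in an earlier trial, not couples declining an offer. The same section reports very high adherence in serodiscordant couples. Couples who see themselves at higher risk may take PrEP more readily.
- **That cost per infection averted inherits the bias.** Objective 3.1.2 rests on its own model.
- **That the two routes contradict each other.** They could give different values; that they will is not shown.

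**Conclusion.** The point holds in this form: section 13.1 fixes a self-selected comparator for the primary measure of objective 3.1.1, and that comparator can show a large benefit, or hide one, when the tools have no effect in the study. At an assumed 90% uptake and 3 per 100 person-years, a 1.5- to 3-fold higher risk in non-users gives a spurious 33 to 67% reduction; the direction is not established. Late starts under ever/never classing could give null rate ratios from about 0.3 (many late starters per never-user, spread over 18 months) up to 1.0. The comparator would hold about 1 to 5 infections at 90 to 95% uptake, but about 5 to 14 at 70%, for 2 to 5 per 100 person-years. Every one of these sizes rests on assumed uptake and incidence. That non-use is the couple's own choice, and that sections 3.1 and 13.1 differ on the outcome and on how infections averted is obtained, needs no assumption.

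**What to change.** Reconcile objectives 3.1.1 and 3.1.2 in section 3.1 with section 13.1 on one outcome and one definition of infections averted. Then:

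- For 3.1.1, use the modelled counterfactual already planned for 3.1.2: expected minus observed infections, with the counterfactual incidence pre-specified and the result shown over a stated range. Use the same number in both objectives.
- Let the baseline risk score inform the expected incidence where possible. Section 11.4 already collects the data, "along with laboratory results to establish the risk score and participant eligibility". The protocol does not say how the score maps to incidence, so that link must be stated as an assumption.
- Keep any user versus non-user comparison descriptive. Treat exposure as time-varying (neither tool; PrEP only; PrEP with ART; ART only), count person-time from the start of each state, and adjust for risk score, index viral load and the covariates listed in 13.1. State how an index partner already on ART at entry (section 7.3) is classed.

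The cost is new wording in sections 3.1 and 13.1, plus modelling that 3.1.2 already requires. The downside is that the result then depends on an external incidence assumption, which is why it must be shown as a range.
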